#### Secondary outcomes

##### Discontinuation

Discontinuation is defined as having a gap of more than 89 days with no medication available within the one year observation period. Cox-proportional hazards will be used to compare discontinuation rates between intervention and control patients.

##### Beliefs about medicines

Patients’ beliefs about medicines will be assessed using the beliefs about medicines questionnaire- specific (BMQs) [25], sent to a random sample of patients three months after the start of therapy. The BMQs assesses both the necessity and concerns regarding prescribed medication. In the questionnaire the name of the specific drug is mentioned in the introduction and wherever it is needed. So for example when a patient starts with simvastatin, one of the BMQ questions will be “I sometimes worry about the long term effects of *simvastatin*”. Five items of the questionnaire assesses the beliefs about the necessity and five items assesses the concerns. Each item of the BMQ is scored using a 5-point Likert scale (1 = strongly disagree, 2 = disagree, 3 = uncertain, 4 = agree, 5 = strongly agree) therefore the individual score ranges from 5 to 25. The results will be expressed as the score on both domains and as the necessity-concerns differential which is the difference between the score on the necessity scale and the concern scale. The results will also be expressed using the two separate scales, divided at the median to generate four attitudinal groups: accepting (high necessity, low concerns), ambivalent (high necessity, high concerns), sceptical (low necessity, high concerns) and indifferent (low necessity, low concerns) [26-28].

##### Satisfaction with information

The satisfaction with information provided by healthcare providers like pharmacists can be assessed with the satisfaction with information about medicines scale (SIMS). As with the BMQ, the name of the specific drug was mentioned in the questionnaire. We used 9 of the 17 items of the original questionnaire [29]. Each item refers to a particular aspect of medicine use. Not all items are used; firstly because some items are not relevant for all four groups of medication, for example “Whether the medication will make you feel drowsy” and “Whether the medication will affect your sex life”. Asking patients these questions when they are not relevant can increase the concerns and thereby influence adherence. Secondly our goal is not to assess the satisfaction in general, but to study the effect of the intervention on satisfaction with information. Thirdly we want to reduce the total number of questions in the questionnaire. We use the items as mentioned in Table 1. We are interested in the effect of the intervention on specific subjects of information and not in an overall satisfaction score. Validation of the combination of the items is therefore not relevant to our study.

**Table 1 T1:** Presentation of selected SIMS items

**Item number**	**SIMS item**	**Original number**
1	How long it will take to act.	5
2	How you can tell if it is working.	6
3	How long you will need to be on your medicine.	7
4	How to get a further supply.	9
5	Whether the medicine has any unwanted effects (side effects)	10
6	What are the risks of you getting side effects.	11
7	What you should do if you experience unwanted side effects	12
8	Whether the medicine interferes with other medicines.	14
9	What you should do if you forget to take a dose.	17
Excluded items:		
	What your medicine is called.	1
	What your medicine is for.	2
	What it does.	3
	How it works.	4
	How to use your medicine.	8
	Whether you can drink alcohol whilst taking this medicine	13
	Whether the medication will make you feel drowsy.	15
	Whether the medication will affect your sex life.	16

Patients are asked to rate the amount of the information received as follows: “too much”, “about right”, “too little”, “none received” and “none needed”. To assess a total satisfaction rating, for each item a score is calculated: if the patient is satisfied (answered “about right”) a score of 1 is given. When the patient is not satisfied (answered “too much”, “too little”, “none needed” or “none received”) this is scored 0. So scores range from 0 to 9, with a high score indicating a high degree of satisfaction. We will calculate a satisfaction score on the same way but based on patients who answered “none received” and “none needed”.

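### The satisfaction score counts *none needed* as dissatisfied, so it cannot separate no need from unmet need, and it is summed to a 0–9 total although the protocol says an overall score is not of interest

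*Protocol article*

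**What the plan says.** All of this is in the protocol article, Secondary outcomes, 'Satisfaction with information'.

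- **Instrument.** "We used 9 of the 17 items of the original questionnaire". For each item the patient rates how much information was received, choosing among *too much*, *about right*, *too little*, *none received* and *none needed*.
- **Item coding.** The rule is that "if the patient is satisfied (answered “about right”) a score of 1 is given". For the other four answers, "When the patient is not satisfied (answered “too much”, “too little”, “none needed” or “none received”) this is scored 0".
- **Total.** The purpose is given as "To assess a total satisfaction rating, for each item a score is calculated", and the result is described thus: "So scores range from 0 to 9, with a high score indicating a high degree of satisfaction".
- **Interest in a total.** Before Table 1 the same subsection says "We are interested in the effect of the intervention on specific subjects of information and not in an overall satisfaction score", and concludes "Validation of the combination of the items is therefore not relevant to our study".
- **Second score.** The closing sentence announces a further score, calculated similarly, that rests on the answers *none received* and *none needed*. It does not say how those answers are to be coded.

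**The concern.** *None needed* reports the absence of a need. *Too little* reports a need left unmet, and *none received* may do so. The coding gives all three the same value and the same label, so neither the item scores nor the total can tell a patient without needs from one whose needs were not met.

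This matters because only the intervention arm receives the extra call, and topics that the call covers, such as side effects and the treatment plan, overlap with the items in Table 1. A patient who needed nothing on a topic, was told about it anyway and found the amount acceptable would move from 0 to 1. That would count as a gain in satisfaction.

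The Background names satisfaction with information and counselling among the main objectives. It adds that the study will assess how far telephone counselling meets patients' needs. A score that merges no need with unmet need serves that purpose poorly.

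There is also an internal conflict. The lack of interest in an overall score is the stated reason for not validating the shortened item set, yet an overall score is then defined and interpreted.

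**Working it through.** **The protocol's own figures.** Nine items scored 0 or 1 give a total from 9 × 0 = 0 to 9 × 1 = 9, as stated. The survey size also reproduces: 2 arms × 100 responses / 0.30 response rate = 667, against a stated minimum of 670 invitations ('Sample size').

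**What the coding does to single patients.**

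| Answer on all nine items | Total, protocol coding | Total if *none needed* = 1 |
|---|---|---|
| *about right* | 9 | 9 |
| *none needed* | 0 | 9 |
| *too little* | 0 | 0 |
| *none received* | 0 | 0 |

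Under the protocol coding an item answered *none needed* can only stay at 0 or rise to 1. If unneeded information makes the answer *about right*, the item gains a point. If it makes the answer *too much*, the item stays at 0. With *none needed* scored 1, the first change would be worth 0 and the second would cost a point.

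**Size of the possible shift.** Let q be the share of item answers that would be *none needed* without the call, and f the share of those that become *about right* with it, all other answers unchanged. Then:

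- change in the proportion satisfied on one item = q × f
- change in the mean total = 9 × q × f
- change in either if *none needed* is scored 1 = 0

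The documents give neither q nor f. For assumed values, the change in the mean total is:

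| q | f = 0.25 | f = 0.50 | f = 1.00 |
|---|---|---|---|
| 0.10 | 0.23 | 0.45 | 0.90 |
| 0.20 | 0.45 | 0.90 | 1.80 |
| 0.30 | 0.68 | 1.35 | 2.70 |

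As f approaches 0, so does the shift.

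**Whether such a shift could be mistaken for an effect.** Take the planned 100 responses per arm, a two-sided 5% comparison of means, no allowance for clustering, and an assumed standard deviation (SD) of the total. The probability of a significant result produced by the shift alone is:

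| Shift | SD 2 | SD 2.5 | SD 3 |
|---|---|---|---|
| 0.45 | 0.36 | 0.25 | 0.18 |
| 0.90 | 0.89 | 0.72 | 0.56 |

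The SDs are assumptions too, and allowing for clustering would lower these probabilities.

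**Item interest against the total.** The text reasons that no overall score is of interest, and therefore that validating the combination is not relevant. It then defines a total and reads it as degree of satisfaction. Once the total is used as an outcome, the stated ground for skipping validation no longer holds. Moving to item-level analysis alone does not cure the coding, because each item carries the same 0/1 rule.

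**The case against.** The strongest reply is that the call is led by need. Under 'Intervention', the pharmacist assesses what information is needed and provides it if necessary. Patients without a need on a topic are those the call is designed not to inform on it, so conversion may be rare. This stands. A reader might infer that the call will move answers and that the result is therefore biased in favour of the intervention. The documents support only that it could. Unneeded information might also turn *about right* into *too much*, which lowers the score, so the net direction of the arm comparison is not fixed. What remains is that the route out of *none needed* can add points and never remove them.

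A reader might also infer that the protocol promises not to use a total. It says only that an overall score is not of interest. The inconsistency is real, but it is not a broken promise.

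The second score need not be a mistake. *None received* and *none needed* differ on need, but both can mean that no information was given, so a count of them might measure non-receipt. The sentence might also define a subgroup. It calls for clarification, and the text does not justify simply striking the score out.

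Finally, scoring *none needed* as 1 is a choice of construct. The question asks about the amount of information received, and someone who received none has, on one view, nothing to rate. Treating the answer as not applicable, or reporting all five categories, would also be defensible. This does not rescue the label of dissatisfied. The published scoring of the original scale is not at hand, and nothing here rests on it.

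**Conclusion.** The point holds for the coding and for the internal conflict, both of which can be read directly from the text. As written, the item scores and the 0–9 total treat no need as dissatisfaction, and a rise in the score need not mean that any unmet need was met.

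The size is not known. The range of about 0.23 to 2.7 points rests wholly on assumed shares of *none needed* (10–30%) and conversion (25–100%) with all other answers unchanged, and it shrinks to nothing if the needs-led call converts almost nobody. It is an illustration and not an estimate of bias.

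This concerns a secondary outcome from a sampled survey. It would be wrong to extend it to the primary adherence outcome or its sample size, neither of which uses these answers.

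**What to change.** 1. Do not count *none needed* as dissatisfied. Score it 1 together with *about right*, as no unmet need, and score *too much*, *too little* and *none received* 0. Keep the protocol's coding as a sensitivity analysis.
2. Make the nine item-level comparisons the main analysis, in line with the stated interest in specific subjects, and present the 0–9 total descriptively only.
3. Report *none received* and *none needed* as separate proportions per item and arm.
4. Clarify the closing sentence on the second score: which answers count as 1, which as 0, in which patients, and what the score is meant to measure.

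The cost is a changed scoring rule and a few sentences of text. The questionnaire already records all five answers, so no new data are needed.

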##### Patient’s experience with counselling

The questionnaire contains 4 items adapted from the consumer quality index (CQI) pharmaceutical care [30,31]. In these items the overall experience of different aspects of counselling related to the new medication, is assessed (see Table 2). In the original CQI the patient can answer on a 4-point Likert scale (“never”, “sometimes”, “often”, and “always”). But since we are only interested in the counselling in the first three months since the start of therapy, patients are offered to indicate “yes”, “no” or “I don’t remember”. Patients reporting they received counselling (answered “yes”) will be scored 1 and patients answering “no” or “I don’t remember” will be scored 0. The total score ranges from 0 to 4.

**Table 2 T2:** Frequency of aspects of counselling (adapted from Consumer Quality Index)

**Item number**	
1	Did a pharmacist or pharmacy-employee ask you about your experiences with *the medication*?
2	Did a pharmacist or pharmacy-employee ask you if you suffered from any side effects?
3	Did the pharmacist or pharmacy-employee provide enough personal counselling?
4	Did the pharmacist or pharmacy-employee ask you if you manage to take your medication as prescribed?

#### Other outcomes

All telephone calls and attempts are registered in a database to monitor the implementation in daily practice. For every call or attempt different aspects are registered:

date and duration of the call, number of attempts, age and gender of patient, reasons for not calling the patient

Early discontinuation: did the patient start with the medication or did he/she decide not to start?

Different aspects of knowledge are assessed by the pharmacist on a 5-point scale “Good”, “Sufficient”, “Poor”, “Bad”, “Not discussed”

Experiences and attitude towards medication are assessed by the pharmacist

Advices given during consultation

Contact with prescribing physician in response to consultation.

### Sample size

Power calculation is focused on the primary outcome, the proportion of adherent patients. With a type one error (α) for a two sided test of 0.05 and a probability of rejecting the null hypothesis of 0.80 (1-β) 294 patients per arm are needed for demonstrating an improvement of the proportion of adherent patients from 70% to 80% [32]. For cluster randomisation a correction is needed based on the Intraclass correlation coefficient (ICC). When using ICC = 0.02 we need at least 15 pharmacies to include at least 30 patients per group of medication for the intervention (4), so 15*30*4 = 1800 patients in the intervention arms and 1800 in the usual care arms. We expect an average response rate of 30% on the questionnaires and with the aim to receive at least 100 responses per arm, we estimated to invite at least 670 patients to participate in the survey.

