## Methods and design

### Study design

We will conduct a multicentre community pharmacy-based, cluster randomized controlled trial (CRT) (Figure 1). Pharmacies are alternately assigned to either group A or group B in a 1:1 ratio. Given the nature of the study design it is impossible for both the researchers and the pharmacists to be blinded to the group assignment. Each group consists of an intervention (TelCIP) arm and a usual care arm. The TelCIP arm in group A focuses on the same medication as the usual care arm in group B and vice versa.

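### The cluster-adjusted minimum of 15 pharmacies × 30 patients is rounded down: it gives about 79% power per medication group, slightly below the stated 80%

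*Protocol article*

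**What the plan says.** The Sample size section of the protocol article bases the calculation on the proportion of adherent patients. The test is specified by "With a type one error (α) for a two sided test of 0.05", the power is 0.80, and the effect is "an improvement of the proportion of adherent patients from 70% to 80"%. Before clustering, "294 patients per arm are needed". The cluster correction follows: "When using ICC = 0.02 we need at least 15 pharmacies to include at least 30 patients per group of medication". The section multiplies this out as 15 × 30 × 4 = 1,800 patients in the intervention arms, and the same number in the usual care arms.

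The abstract and the section on recruitment of patients plan 30 pharmacies. The Study design section allocates them 1:1 to groups A and B, which leaves 15 per group. It adds: "Each group consists of an intervention (TelCIP) arm and a usual care arm". For any one medication group, TelCIP patients therefore come from the 15 pharmacies of one group and usual care patients from the 15 of the other. The article does not print the design-effect formula or the rounding step.

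**The concern.** The paragraph gives all the inputs that a standard design-effect calculation needs, so its result can be checked. A number introduced as a minimum should be rounded up. Here the result lies between 15 and 16 pharmacies and the plan gives 15.

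The factor of 4 in the product shows that 15 × 30 is meant to serve each medication group separately. The Discussion also counts on adequate numbers in all four medication groups to learn who benefits most. At stake is whether the stated 80% power is true of that comparison. Because 30 pharmacies are planned, the number per group equals the understated minimum, and only the number of patients per pharmacy can make up the difference.

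**Working it through.** **Inputs**, all from the Sample size section: two-sided α = 0.05 (z = 1.960); power 0.80 (z = 0.842); proportions 0.70 and 0.80 (mean 0.75); ICC = 0.02; m = 30 patients per pharmacy per medication group; k = 15 pharmacies per arm, which agrees with 30 pharmacies allocated 1:1.

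**1. Size before clustering.** With the pooled variance under the null hypothesis:

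n = [1.960 × √(2 × 0.75 × 0.25) + 0.842 × √(0.70 × 0.30 + 0.80 × 0.20)]² / 0.10² = 293.2, rounded up to 294.

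The plan's 294 reproduces.

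**2. Design effect.** DE = 1 + (m − 1) × ICC = 1 + 29 × 0.02 = 1.58.

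**3. Size after clustering.** 294 × 1.58 = 464.5, so 465 patients per arm per medication group. Divided by 30, this is 15.48 pharmacies, so 16.

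**4. What the plan states.** 15 × 30 = 450, which is 15 patients (3.2% of 465) short. The effective size is 450 / 1.58 = 284.8, against 294 needed.

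**5. Power at 15 × 30, normal formula.**

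- Pooled variance: (0.10 × √284.8 − 1.960 × √0.375) / √0.37 = 0.80, which gives 78.9%.
- Unpooled variance: 0.10 / √(0.37 / 284.8) − 1.960 = 0.81, which gives 79.2%.

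**6. Does another usual formula lead to 15?**

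| Formula for the size before clustering | n | n × 1.58 | Pharmacies of 30 |
|---|---|---|---|
| Pooled (gives the plan's 294) | 294 | 464.5 | 15.48 |
| Unpooled | 290.4 | 458.8 | 15.29 |
| Arcsine | 291.7 | 460.9 | 15.36 |
| Continuity-corrected | 313 | 494.5 | 16.48 |

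None gives 15 or fewer, and among these only the pooled formula gives 294.

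**7. Combinations that meet 294.** With 15 pharmacies, 15m / (1 + 0.02(m − 1)) ≥ 294 gives 9.12m ≥ 288.12, so m ≥ 31.6, that is 32.

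| Pharmacies × patients | DE | Effective n | Power (normal, pooled) |
|---|---|---|---|
| 15 × 30 | 1.58 | 284.8 | 78.9% |
| 15 × 31 | 1.60 | 290.6 | 79.7% |
| 15 × 32 | 1.62 | 296.3 | 80.4% |
| 16 × 30 | 1.58 | 303.8 | 81.4% |

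**8. Sensitivity, not a correction that the plan states.** With 15 pharmacies per arm, a t reference has 2 × 15 − 2 = 28 degrees of freedom. Power at 15 × 30 is then 76.4% (noncentral t, unpooled variance).

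**The case against.** The strongest reply is that this is rounding. One percentage point of power is less than the uncertainty in an ICC given to one significant figure: an ICC of (450/294 − 1)/29 = 0.0183 would make 15 × 30 exactly enough, and it rounds to 0.02. With the unpooled formula the requirement is 459, within 2% of 450. The article condenses a fuller protocol, and 15 and 30 are both worded as minimums, so two more patients per pharmacy close the gap. All of this stands and limits the point to a minor one. It does not remove it: the printed inputs are 294 and 0.02, and they do not give 15.

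A reader might infer more than the document supports, in four ways.

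- **That the trial as a whole is underpowered.** The shortfall concerns comparisons within one medication group. Pooled over all four, 1,800 per condition has an effective size of 1,800 / 2.18 = 825.7 if counted as 30 clusters of 60 (99.7% power), or 1,800 / 3.38 = 532.5 if counted as 15 clusters of 120 (96.6%).
- **That the plan contradicts itself by ignoring the small number of clusters.** The article states no t reference, and a normal-formula design effect is common practice. The 76% is a sensitivity figure.
- **That unequal pharmacy sizes lower the power further.** The article gives no figure for their variation, and it asks every pharmacy for at least 30. If all reach that number, sizes vary only upwards.
- **That the survey figure in the same paragraph is also wrong** ("with the aim to receive at least 100 responses per arm, we estimated to invite at least 670 patients to participate in the survey"). It reproduces: 670 × 0.30 = 201, or 100 in each of two arms, and the Follow up section also speaks of two arms. No power is claimed for it. At most the word arm could be clearer.

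**Conclusion.** The point holds as a minor arithmetic correction. On the plan's own inputs, 465 patients (16 pharmacies of 30) are needed per arm per medication group. The stated minimum of 15 × 30 = 450 gives an effective size of about 285 and about 79% power instead of 80%.

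This rests on the usual design effect with equal pharmacy sizes, the stated ICC of 0.02, and the reading that 15 × 30 serves each medication group, which the multiplication by 4 supports. No design or analysis decision depends on it.

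**What to change.** Reword the cluster-correction sentence, show the design effect of 1.58, say that the power applies to each medication group, and take one of two routes.

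1. Keep 15 pharmacies × 30 patients and state about 79% power per medication group, with about 76% as a sensitivity figure under a t reference on 28 degrees of freedom. The cost is a slightly less favourable stated figure.
2. State the minimum as 32 patients per pharmacy per medication group. This gives 15 × 32 = 480 per arm per medication group and 80.4% power by the normal formula. The total becomes 15 × 32 × 4 = 1,920 per condition, 120 more in each, with no additional pharmacies. Under the t reference it is about 78%, so the text should name the formula that the 80% refers to.

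Sixteen pharmacies of 30 per group would also do (81.4% by the normal formula), but needs 32 pharmacies where 30 are planned. Either numbered route is the lighter change.

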### Statistical analysis

The primary analysis is based on the intention-to-treat (ITT) principle e.g. in the intervention group all patients who should have received the intervention will be included. Patient characteristics between groups will be compared using Student’s t-test or χ^2^- test. Because it is likely that the PDC360 will not be normally distributed, PDC360 differences between groups will be compared using the nonparametric Mann–Whitney U test. We use logistic multilevel analysis to study the effect on the dichotomous primary outcome (adherent yes or no). The outcome of complete discontinuation will be assessed using Cox-proportional hazards. We consider a p-value of less than 0.05 to be statistical significant. In a second analysis effect modification and confounding will be assessed. Effect modification is defined as a significant interaction (p < 0.10) between group allocation and the variable in question. In a per-protocol (PP) analysis we include in the intervention group only patients who actually received the call.

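### Continuous PDC360 is tested with a Mann–Whitney U test that ignores pharmacy, and Cox regression for discontinuation is named with no pharmacy term, although pharmacies are the allocated unit

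*Protocol article*

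**What the plan says.** The protocol article assigns pharmacies, not patients, to group A or B in a 1:1 ratio (Study design). Its Sample size section states that "For cluster randomisation a correction is needed based on the Intraclass correlation coefficient (ICC") and uses an ICC of 0.02 with 15 pharmacies and 30 patients per pharmacy per medication class.

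The Statistical analysis section then treats the three adherence results differently:

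- Adherent yes or no: multilevel logistic regression.
- Continuous PDC360: "PDC360 differences between groups will be compared using the nonparametric Mann–Whitney U test". The reason given is expected non-normality.
- Discontinuation: "The outcome of complete discontinuation will be assessed using Cox-proportional hazards". The Discontinuation section has similar wording: "Cox-proportional hazards will be used to compare discontinuation rates between intervention and control patients".

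All are judged by one rule: "We consider a p-value of less than 0.05 to be statistical significant". The Primary outcome section says that refill adherence will be analysed in both its continuous and its dichotomous form, so continuous PDC360 sits under the primary outcome heading.

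**The concern.** A Mann–Whitney U test in its standard form assumes independent observations. Patients of one pharmacy share staff, counselling habits and catchment area. The document expects such differences itself: its Limitations section does not rule out baseline differences in level of care between pharmacies, and its Discussion expects pharmacists to differ in how they deliver the call. The reason given for the rank test deals with the shape of the distribution and not with dependence.

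The same dispensing data would therefore be tested once with clustering and once without. A significant PDC360 or persistence result could stand beside a non-significant multilevel result purely because of the method, and readers could take it as supporting evidence.

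**Working it through.** **Inputs from the Sample size section.** Two-sided alpha 0.05, power 0.80, adherence 70% against 80%, ICC 0.02, 15 pharmacies, m = 30 patients per pharmacy per class. That gives 15 × 30 = 450 patients per arm per class.

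**The plan's own figure.** n = [1.960 × √(2 × 0.75 × 0.25) + 0.842 × √(0.21 + 0.16)]² / 0.10² = 293.2, rounded up to 294 per arm. This reproduces the stated 294. Inflated for clustering, 294 × 1.58 = 465, or 15.5 pharmacies of 30. This is close to the stated 15 and shows that the trial is sized per medication class.

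**Within a class, each pharmacy is in one arm only.**

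- Design effect: 1 + (m − 1) × ICC = 1 + 29 × 0.02 = 1.58.
- Standard error understated by √1.58 = 1.26.
- Effective sample size: 450 / 1.58 = 285 per arm.
- Actual type I error of an unadjusted test: 2 × [1 − Φ(1.96 / √1.58)] = 11.9%. The critical |z| would have to be 1.96 × 1.26 = 2.46.

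The ICC of 0.02 was chosen for the dichotomous outcome. The document gives none for PDC360 or discontinuation, so the ICC is an assumption here. Same formula, m = 30:

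| ICC | Design effect | Type I error |
|---|---|---|
| 0.005 | 1.145 | 6.7% |
| 0.01 | 1.29 | 8.4% |
| 0.02 | 1.58 | 11.9% |
| 0.03 | 1.87 | 15.2% |
| 0.05 | 2.45 | 21.1% |

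At ICC 0.02, m = 20 gives 9.5% and m = 60 gives 18.4%.

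**Check by simulation under the null** (15 against 15 pharmacies, 30 patients each, ICC 0.02, 6,000 runs). With a skewed PDC-like outcome capped at 1, the Mann–Whitney U test rejected in 11.6% of runs and a t-test on pharmacy means in 4.9%. For discontinuation, the log-rank test (the Cox score test) rejected in 11.8% to 12.4%, with one-year discontinuation assumed at 20% to 50%.

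**Pooled over four classes, each pharmacy supplies patients to both arms.** Let ρ be the share of the pharmacy variance that is common to all classes. The common part cancels between arms, so the ratio of true to assumed variance is (1 − ICC) + m × ICC × (1 − ρ), taking mean PDC360 to be equal across classes.

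| ρ | Variance ratio | Type I error, formula | Simulation, 2,000 runs |
|---|---|---|---|
| 1 (fully shared) | 0.98 | 4.8% | 4% |
| 0.5 | 0.98 + 0.30 = 1.28 | 8.3% | 8.7% |
| 0 (class-specific) | 0.98 + 0.60 = 1.58 | 11.9% | 10.7% |

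The gaps between the last two columns are within simulation error: √(0.107 × 0.893 / 2000) = 0.7 percentage points in the bottom row.

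**The case against.** The strongest reply is that the comparison on which the trial is powered is already protected. The primary outcome is the proportion of adherent patients, and its multilevel logistic model accounts for pharmacy. This stands. A reader might infer that the trial's main conclusion is at risk, and the document does not support that. What remains is the continuous form of the measure and one secondary outcome.

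Second, a reader might take 12% as the error rate of the planned tests. The Statistical analysis section speaks only of differences between groups and does not say whether they are tested per class or pooled. Class-level testing is a fair inference from the sizing and from the Discussion's aim of learning which patients in the four medication groups benefit most, but it is not stated. Nor is an ICC given for these two outcomes. The 12% is therefore conditional, and pooling with a fully shared pharmacy effect would leave the error near nominal.

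Third, the Cox point rests partly on silence. A frailty term or clustered variance fits within a Cox model, and an article may leave that to the full plan. The explicit use of a multilevel model in the same paragraph suggests that none was intended, but does not prove it. The Mann–Whitney point is different: a specific test is named that has no place for pharmacy, so a later plan would have to contradict it.

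Finally, one might extend the criticism to the baseline t-tests and χ² tests. Nothing in the document makes those p-values decide the effect estimate or the choice of covariates. Whether to report them is a matter of preference and not part of this point.

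**Conclusion.** The point holds for continuous PDC360: as written, the test does not match the allocation, and the document's own reasoning on sample size says why. For class-level tests the type I error is about 12% under the planning values (ICC 0.02, m = 30), and above 5% at every ICC examined. For pooled tests it lies between roughly nominal and the class-level figure. The pooled case can come out near 5%, but only if pharmacy effects are the same across four quite different drug classes, which nothing in the document establishes.

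For discontinuation the same figures apply if the Cox model is fitted without a pharmacy term. Confidence in that part is moderate. This should be fixed before analysis, but it does not undermine the primary dichotomous comparison.

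**What to change.** State whether PDC360 and discontinuation are compared per class, pooled, or both, and replace the Mann–Whitney U test accordingly:

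- **Within a class:** a cluster-level analysis of pharmacy means or mean ranks, or a cluster-adjusted rank test.
- **Pooled:** within-pharmacy contrasts between arms, adjusted for class, or a mixed model with pharmacy and pharmacy-by-class effects and inference that is robust to non-normality. A two-sample t-test on pharmacy means does not suit the pooled case, because the same pharmacies appear in both arms.

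For discontinuation, state that the Cox model uses a shared pharmacy frailty or a pharmacy-clustered robust variance. If a fuller plan already says so, a cross-reference is enough.

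The change needs no new data and no change to recruitment. The cost is usually wider confidence intervals in class-level comparisons, by a factor of about 1.26 at the planning ICC.
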